### Quantitative analysis

The analysis population will include all randomized patients. Patients will be analyzed according to their assigned intervention group, regardless of what treatment they receive (intent to treat analysis). Descriptive statistics (mean and standard deviation) will be used to summarize the distribution of the primary outcome (loneliness), and secondary outcomes (opioid misuse, depression, anxiety, functionality and opioid dose) at baseline, immediately following the intervention and 3 months following the intervention. Linear mixed models will be used to test the association between the intervention arm and the change in the primary outcome and secondary outcomes across the study period. Since we expect that the effect from the intervention takes places immediately after implementation, we will include the intervention arm (control arm as the reference), an indicator for the post-treatment time points (immediately following the intervention and 3 months after) as well as their interaction as independent variables. Intervention assignment will be modeled as a fixed effect, and individual participants will be modeled as a random effect. Each model will contain a random intercept to account for the subject-specific correlation in outcome. In a secondary analysis, we will add a contrast variable to test the maintenance of outcomes between the second and third time points.

Subgroup analyses, which will be exploratory in nature, will be performed using the same modeling technique to assess the heterogeneity of treatment effects across subgroups of patients defined by age (grouped by tertiles), gender (male, female and nonbinary), rurality (rural urban continuum codes), initial opioid MME (calculated using the Centers for Disease Control and Prevention’s data file on opioid analgesic morphine milligram equivalents and grouped by tertiles) and initial loneliness score (grouped by tertiles).

Missing data mechanisms will be examined by correlating the proportion of missing data with key baseline characteristics. Multiple imputation by chained equations will be applied to account for loss-to-follow-up. Inferences will be drawn based on two-sided *p*-value of 0.05. Given that all participants are randomly assigned to one of the three intervention arms, we do not expect substantial bias in unadjusted analysis results. Hence, we do not plan to include control variables in our statistical modelling.

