### Study intervention platform

Each active intervention (CBT and social prescribing) will consist of eight one hour, weekly group based sessions delivered via telehealth. Each group will consist of 6–10 participants using a HIPAA-compliant zoom platform allowing group members to see and hear each other.

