### Power analysis

We plan to recruit 102 patients on long-term opioid therapy based on a sample size calculation allowing us to detect 6-point changes or more in the UCLA loneliness scale (Version 3). The 6-point change was determined by the mean loneliness score change from a previously published meta-analyses of psychological interventions for loneliness [31]. For the sample size calculation, we also assumed a significance level of 0.05, a desired power of 0.80, and a standard deviation of 8.0 (from weighted average from the original validation of the UCLA loneliness scale). Based on this, we will require 28 patients per arm. Assuming an 80% retention rate, we plan to recruit 34 patients per arm (or 102 patients total).

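### Both active arms are delivered in groups of 6–10, but the planned model and the sample size treat participants as independent, so standard errors for every active-arm contrast are too small if outcomes correlate within groups

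*Protocol article*

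**What the plan says.** Under Study intervention platform, both active interventions run as eight weekly one-hour telehealth sessions. On their size the text says: "Each group will consist of 6–10 participants". Members can see and hear one another. Under Usual care, participants in the third arm continue care individually and receive a handout, so that arm has no groups.

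Quantitative analysis sets out the model. The fixed terms are arm, a post-treatment indicator covering both follow-up times, and their interaction. On correlation it says "Intervention assignment will be modeled as a fixed effect, and individual participants will be modeled as a random effect", followed by a subject-level random intercept. No therapy-group term appears, and clustering by group is mentioned nowhere in the article.

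Power analysis targets a 6-point difference on the UCLA Loneliness Scale and continues: "we also assumed a significance level of 0.05, a desired power of 0.80, and a standard deviation of 8.0". It concludes: "Based on this, we will require 28 patients per arm". Inflation for dropout gives 34 per arm. No ICC or design effect is given.

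**The concern.** Participants are randomized individually, but in two of three arms they are then treated together. This is a partially nested design. The treatment works through social contact and the primary outcome is loneliness, so members of one group may plausibly end up more alike than members of different groups. A participant random intercept handles repeated measurements on one person. It does not handle correlation between people.

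If that correlation is positive, group-level variation is counted as independent evidence. The estimates stay unbiased, but confidence intervals are too narrow and false-positive claims more frequent than stated. This affects the primary test of each intervention against usual care. It affects CBT versus social prescribing more, because both of those arms are clustered. That comparison carries the stated noninferiority hypothesis, and an interval that is too narrow makes noninferiority too easy to claim.

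This is not a detail left to an analysis plan, because the article specifies the correlation structure.

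**Working it through.** **Inputs from the article.** Difference 6, SD 8.0, two-sided alpha 0.05, power 0.80, 28 evaluable per arm (Power analysis; Quantitative analysis); groups of 6–10 (Study intervention platform).

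**Assumptions.** ICC 0.02–0.10; m = 7–8 evaluated members per group (28/7 = 4 groups per active arm).

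**1. The article's own figure.** n = 2(1.96 + 0.842)² × 8²/6² = 27.9, rounded up to 28. Power at 28 = Φ(6/√(2 × 64/28) − 1.96) = Φ(2.806 − 1.96) = 80.1%. The stated figure therefore contains no allowance for clustering.

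**2. With clustering, on the same two-sample basis.**
- Design effect in an active arm: DE = 1 + (m − 1) × ICC; in usual care DE = 1.
- Ratio of true to assumed variance: (DE + 1)/2 against usual care; DE for CBT versus social prescribing.
- True type I error of the unclustered test: 2(1 − Φ(1.96/√ratio)).
- Power against usual care: Φ(6/√((64/28)(1 + DE)) − 1.96).

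| ICC | DE (m = 7 / 8) | Type I vs usual care | Type I, CBT vs social prescribing | Power vs usual care |
|---|---|---|---|---|
| 0.02 | 1.12 / 1.14 | 5.7 / 5.8% | 6.4 / 6.6% | 77.8 / 77.4% |
| 0.05 | 1.30 / 1.35 | 6.8 / 7.1% | 8.6 / 9.2% | 74.4 / 73.5% |
| 0.10 | 1.60 / 1.70 | 8.6 / 9.2% | 12.1 / 13.3% | 69.2 / 67.6% |

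Worked line, ICC 0.05 and m = 7: DE = 1 + 6 × 0.05 = 1.30; ratio = 1.15; 1.96/√1.15 = 1.828, so type I error is 6.8%. Power = Φ(6/√(2.286 × 2.30) − 1.96) = Φ(0.657) = 74.4%.

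At ICC 0.05, the ends of the stated group size (m = 6 and 10) give type I error of 6.5% and 7.7% and power of 75.4% and 71.8% against usual care.

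**3. The planned contrast.** With complete data, the arm-by-post interaction compares arms on the mean of two follow-up scores minus baseline. With a common within-person correlation ρ, its variance per person is 1.5(1 − ρ) × SD². This equals SD², the basis of the stated calculation, when ρ = 1/3. Take ρ = 0.5, an assumption: the variance is 0.75 SD², and clustering at follow-up raises the active-arm value to (0.75 + (m − 1) × ICC) SD².

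| ICC | Type I vs usual care (m = 7 / 8) | Type I, CBT vs social prescribing | Power vs usual care |
|---|---|---|---|
| 0 | 5.0% | 5.0% | 90.0% |
| 0.02 | 5.9 / 6.1% | 6.9 / 7.2% | 87.7 / 87.3% |
| 0.05 | 7.4 / 7.8% | 9.8 / 10.6% | 84.1 / 83.1% |
| 0.10 | 9.8 / 10.6% | 14.4 / 15.9% | 78.2 / 76.3% |

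A 20,000-replicate simulation of this contrast (4 groups of 7, ρ = 0.5) agreed. Type I error was 7.8% and 10.4% at ICC 0.05, and 10.3% and 15.5% at ICC 0.10, for the two comparisons in that order.

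**4. Degrees of freedom.** A correct analysis rests on few groups. On the two-sample basis with 4 groups of 7, Satterthwaite df = (DE + 1)²/(DE²/3 + 1/27), which is 9.9, 8.8 and 7.6 at ICC 0.02, 0.05 and 0.10. Power from the noncentral t distribution is then about 69%, 64% and 57%.

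**The case against.** A reader might infer that the trial does not deliver its stated 80% power. The documents do not support that as a fact. They give neither an ICC nor a within-person correlation. The planned model uses baseline and two follow-up scores, which the sample-size formula ignores. At ρ = 0.5 its power stays above 80% at ICC 0.05 by the normal approximation and falls below only towards ICC 0.10. A ρ below 1/3 would reverse this. The power half of the point is therefore conditional.

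The size of the error also depends on an assumed ICC. At ICC 0.01, two-sample power falls by only 1–2 points and type I error against usual care is about 5.4%. More, smaller groups also reduce the effect: five groups per arm (28/5 = 5.6 members) at ICC 0.05 give type I error of 6.3%.

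Two further inferences should not be drawn. The article does not say whether group membership is closed or rolling. A shared interventionist also does not by itself create variation between groups: if one person leads every group in an arm, that influence is common to the arm.

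The standard-error point stands. Better use of baseline recovers power but does not protect type I error, which at ρ = 0.5 is slightly higher than on the two-sample basis.

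**Conclusion.** The concern holds for the standard errors. The design creates groups in two arms, the specified model ignores them, and any positive within-group correlation makes the active-arm standard errors too small. For ICC 0.02–0.10 and 7–8 per group, type I error at nominal 5% is about 6–9% against usual care and 6–13% between the two interventions. With within-person correlation 0.5 in the planned contrast, the ranges are about 6–11% and 7–16%.

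The loss of power is real on the article's own calculation (77–78%, 74% and 68–69% at ICC 0.02, 0.05 and 0.10, before any loss of degrees of freedom). It is not proven for the planned model. All magnitudes rest on assumed ICC, group size and within-person correlation; only the direction of the standard-error problem does not.

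**What to change.** Record each participant's assigned therapy group. In Quantitative analysis, add a therapy-group random effect on the post-treatment records of the two active arms, with zero group variance in usual care. Define groups by assignment so that intention to treat is kept, and use Satterthwaite or Kenward-Roger degrees of freedom. Fix this before results are seen.

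In Power analysis, state that 80% assumes no clustering by therapy group. Then give power for the analysis actually planned over a stated range of ICC and within-person correlation, including the small-sample degrees of freedom. A single replacement range such as 68–78% should not be written in, because it ignores both the baseline correlation and the degrees of freedom that the corrected analysis uses up.

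The cost is one recorded variable, one model term, wider intervals and possibly a less favourable stated power. No extra patients are needed. With only a handful of groups per arm, the group variance will be imprecisely estimated.

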### Participant eligibility

We will recruit patients who are on long-term opioid therapy (defined as ≥ 3 months receiving prescribed opioids [functional definition is ≥ 3 opioid prescriptions each ≥ 21 days apart]) and who meet the following inclusion criteria: English-speaking, 18 years of age or older and score 6 or greater on the 3-item UCLA-loneliness scale (the scale is scored from 3 to 9). The 3-item scale will be used for eligibility while the 20-item scale will be used for outcomes. We will exclude patients who have active cancer, active psychosis, or moderate/severe cognitive impairment using the mini-MOCA, are on palliative care or live in a controlled setting (i.e., assisted living, nursing home or inpatient treatment facility).

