### Effectiveness outcomes

The effectiveness outcomes will be assessed at baseline, at completion of the intervention (at 8 weeks) and at 3 months following the completion of the intervention.

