### Data collection

We will collect the outcome measures from patients in the week post intervention and 3 months post intervention (or for those in the usual care arm 10 weeks after initial data collection and then 3 months following that). Data collection will take place via phone, email or mail depending on the patient preference indicated in their baseline data collection. Patients will be given a $50 gift card incentive for each data collection time point.

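### A random intercept as the only within-patient correlation term makes the standard error of the pooled pre/post effect depend on an unverified equal-correlation assumption; the direction and size of the error are uncertain

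*Protocol article*

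**What the plan says.** The Effectiveness outcomes section of the protocol article sets three measurement times: "The effectiveness outcomes will be assessed at baseline, at completion of the intervention (at 8 weeks) and at 3 months following the completion of the" (cut one word short here). The Data collection section gives a slightly different timing for controls: "for those in the usual care arm 10 weeks after initial data collection and then 3 months following that".

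The Quantitative analysis section specifies linear mixed models with arm, "an indicator for the post-treatment time points (immediately following the intervention and 3 months after) as well as their interaction as independent variables". One indicator thus covers both follow-ups, and baseline is part of the outcome vector. On correlation within a patient the section says: "Each model will contain a random intercept to account for the subject-specific correlation in outcome". It names no residual covariance structure, random slope or robust standard error. Testing is fixed by "Inferences will be drawn based on two-sided *p*-value of 0.05".

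**The concern.** A random intercept with independent residuals allows one variance and one correlation for all pairs of visits. The primary effect, arm by post-treatment, is the mean of the two follow-ups minus baseline, compared between arms. The model estimates the variance of that contrast by averaging two pieces of within-person information: pre versus post, and 8 weeks versus 3 months. Only the first bears on the primary effect. If the two pieces differ in variability, the reported standard error is wrong, even with complete data and no clustering by therapy group.

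The p-values and confidence intervals for the UCLA score, the COMM and the other continuous outcomes are at stake. So is the interval for CBT versus social prescribing, on which the noninferiority hypothesis in the Hypothesis section would rest.

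**Working it through.** **The plan's own figure.** The Power analysis section states: "we also assumed a significance level of 0.05, a desired power of 0.80, and a standard deviation of 8.0". With a 6-point difference, n = 2(1.96 + 0.842)² × 8² / 6² = 27.9, so 28 per arm, as stated. This is a two-sample comparison at SD 8. It does not use the mixed model, so nothing below changes it.

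**Inputs.** SD s = 8 and 28 evaluable patients per arm come from the Power analysis section. The correlations r01 and r02 (baseline with each follow-up) and r12 (between follow-ups) are assumptions, because the document gives none.

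**Formulas** (complete data, equal variances, per patient):

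- True variance of mean(post) − baseline: s²[1.5 + 0.5 r12 − (r01 + r02)]
- Variance reported by the random-intercept model: s²[1.5 − 0.5(r01 + r02 + r12)]
- True minus reported: s²[r12 − (r01 + r02)/2]
- SE of a two-arm difference: √(2 × variance / 28)
- Approximate type I error: 2[1 − Φ(1.96 × reported SE / true SE)]

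The reported SE is right when r12 = (r01 + r02)/2, too small when r12 is larger and too large when r12 is smaller.

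**Example, 0.5/0.5/0.7.** The true factor is 1.5 + 0.35 − 1.0 = 0.85, giving SE √(2 × 64 × 0.85 / 28) = 1.97. The reported factor is 1.5 − 0.85 = 0.65, giving SE 1.72. The ratio is 0.87 and the type I error 8.7%.

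| r01 / r02 / r12 (assumed) | r12 − (r01+r02)/2 | Reported SE | True SE | Ratio | Type I error |
|---|---|---|---|---|---|
| .7 / .6 / .6 | −0.05 | 1.59 | 1.51 | 1.05 | 4.0% |
| .6 / .6 / .6 | 0 | 1.66 | 1.66 | 1.00 | 5.0% |
| .7 / .5 / .6 | 0 | 1.66 | 1.66 | 1.00 | 5.0% |
| .6 / .55 / .65 | 0.075 | 1.66 | 1.76 | 0.94 | 6.5% |
| .6 / .6 / .7 | 0.10 | 1.59 | 1.72 | 0.92 | 7.1% |
| .6 / .5 / .7 | 0.15 | 1.66 | 1.85 | 0.89 | 8.0% |
| .5 / .5 / .7 | 0.20 | 1.72 | 1.97 | 0.87 | 8.7% |
| .6 / .6 / .8 | 0.20 | 1.51 | 1.79 | 0.85 | 9.8% |
| .5 / .5 / .8 | 0.30 | 1.66 | 2.03 | 0.82 | 11.0% |

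Simulation (10,000 trials per setting, three arms of 28) agrees: 8.3% at .5/.5/.7, 10.1% at .6/.6/.8 and 3.8% at .7/.6/.6. Fitted mixed models at .5/.5/.7 gave a mean SE of 1.71 against an empirical SD of 1.94.

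**Pure decay with time.** The gaps are about 9 or 10 weeks, then 13 weeks. Correlation falling steadily with the gap gives ratios of 0.95 to 1.00 and type I error of 5.0% to 6.3%.

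**Narrower baseline.** Take all correlations at .6, baseline SD 7 and follow-up SD 8. The true variance is 49 + 51.2 − 67.2 = 33.0. The reported variance is 1.5 × (59 − 35.2) = 35.7. The ratio is 1.04 and the type I error about 4.2%.

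**Lasting differences in response.** Assume correlations of .6, SD 8, and a person-specific step change with SD τ in the two active arms, the same at both follow-ups. The contrast variance is 64 × 0.6 = 38.4 in usual care and 38.4 + τ² in each active arm. The model, pooling all arms and both pieces of information, reports 38.4 + τ²/3. The true average is 38.4 + τ²/2 for active versus usual care and 38.4 + τ² for CBT versus social prescribing.

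| τ (assumed) | Reported variance | True, active v usual care | Type I error | True, CBT v social prescribing | Type I error |
|---|---|---|---|---|---|
| 3 | 41.4 | 42.9 | 5.4% | 47.4 | 6.7% |
| 6 | 50.4 | 56.4 | 6.4% | 74.4 | 10.7% |

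**The case against.** A reader might infer that the standard error simply is too small. The document does not support that. It reports no correlations, and the schedule does not make the follow-ups the closest pair in time: the first comes 8 to 10 weeks after baseline, the second about 13 weeks after the first. A set such as .5/.5/.7 assumes the stronger correlation across the longer gap. Spacing alone gives at most 6.3% in the settings tried. This objection stands, and it makes the point conditional.

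A reader might also think that selecting patients on a high short-form loneliness score (Participant eligibility section) makes matters worse by lowering correlations with baseline. It also shrinks the baseline variance, and the net effect runs the other way. In 18 simulated selection settings type I error was always below 5%, at 3.3% to 4.7%.

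Differences in response arise only where treatment does something. If treatment affects nobody, this mechanism is absent. The error rates in the last table are for a null of no average difference. For CBT versus social prescribing, that null is compatible with both treatments working unevenly across people.

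Finally, a random intercept over three visits is conventional, and an analysis plan that is not shown may add a residual structure or robust errors. That is possible. The article nevertheless states a correlation model rather than leaving it open, and as stated it has this weakness.

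**Conclusion.** The point holds conditionally. With independent residuals, the published model gives a correct standard error for the pooled effect (equal variances) only when r12 equals the mean of r01 and r02. In the assumed sets where r12 exceeds that mean by roughly 0.1 to 0.3, the SE is about 6% to 18% too small. The direction is not established by the document, and neither is the size. The mechanism that fits the article's own expectation of an immediate effect, with planned subgroup analyses of uneven response, is a lasting step change that varies between people. Under the assumed response SDs this matters little for active versus usual care and more for CBT versus social prescribing. The reason to act is that validity need not rest on an unverified assumption that is cheap to remove.

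**What to change.** Replace the random-intercept-only structure with an unstructured 3x3 within-person covariance, fitted by REML with Kenward-Roger degrees of freedom, or with equivalent small-sample degrees of freedom after the planned multiple imputation. Alternatively, keep the random intercept and base inference on small-sample-corrected robust standard errors. Apply the choice to all continuous outcomes. Basing the SE on each patient's own change score, which is what an unstructured covariance amounts to for the equally weighted contrast with complete data, held type I error at 4.8% to 5.3% in all six simulated settings.

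The cost is one line in the analysis plan and a few more variance parameters (six in all for three visits). There are two side effects to settle:

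- With a single post-treatment indicator, an unstructured covariance may weight the two follow-ups unequally. If equal weights are intended, model the visits separately and average them.
- A covariance shared by all arms only partly covers response differences confined to the active arms. At τ = 6 it reports 38.4 + (2/3) × 36 = 62.4 against a true 74.4 for CBT versus social prescribing, a type I error of about 7.3%. Robust errors or arm-specific covariances avoid this.

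### The primary model uses the baseline score in a difference in differences and bars covariates; this is unbiased but gives up precision that baseline adjustment would recover at almost no cost

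*Protocol article*

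**What the plan says.** All of this is in the protocol article. Under Effectiveness outcomes, the measures are "assessed at baseline, at completion of the intervention (at 8 weeks) and at 3 months following the completion of the intervention". Under Quantitative analysis, the fixed effects are specified: "we will include the intervention arm (control arm as the reference), an indicator for the post-treatment time points" (one indicator covers both follow-ups), "as well as their interaction as independent variables". The covariance is also specified: "Each model will contain a random intercept to account for the subject-specific correlation in outcome".

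Covariates are then excluded. The ground is that, because arms are randomly assigned, "we do not expect substantial bias in unadjusted analysis results". The next sentence reads "Hence, we do not plan to include control variables in our statistical modelling".

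The Power analysis section takes a 6-point effect, an SD of 8.0, significance level 0.05 and power 0.80. It arrives at 28 patients per arm, raised to 34 per arm (102 in total) for 80% retention. It gives no correlation between visits and no SD of change.

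**The concern.** With arm, post and arm x post in the model, the arm main effect estimates a baseline difference that randomisation already makes zero in expectation. The interaction then equals the between-arm difference in mean change from baseline. A change score subtracts the whole baseline value. The best linear use of baseline subtracts only the part that predicts follow-up. The difference between the two is added noise.

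The article's argument for leaving out covariates is correct about bias, but baseline adjustment in a randomised trial is done for precision. Precision matters here because arms are small (34 recruited, about 28 analysed). Several secondary outcomes, including opioid misuse, are to be tested with the same model, and no power is stated for them.

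**Working it through.** **Inputs from the article.** Effect 6 points, SD 8.0, two-sided 0.05, 28 per arm, one baseline visit and two follow-ups, a random intercept only.

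**Assumed, because the article does not give it.** One common correlation rho between any two visits (compound symmetry, as the random intercept implies), equal SDs at all visits unless stated otherwise, and complete data. I use rho = 0.3, 0.5 and 0.7.

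**Step 1: the plan's own figure.** n per arm = 2 x (1.96 + 0.84)^2 x 8^2 / 6^2 = 27.9, so 28, with power 0.801. The stated 28 reproduces. It is a two-arm comparison at a single visit with no baseline term, so its variance factor, in units of 2 x SD^2/n, is 1.

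**Step 2: variance factors in the same units.**
- Planned contrast, mean of two follow-ups minus baseline: (1+rho)/2 + 1 - 2rho = 1.5(1-rho).
- Baseline-adjusted mean of two follow-ups: (1+rho)/2 - rho^2 = (1-rho)(1+2rho)/2.
- Share of attainable precision lost: 1 - (1+2rho)/3 = 2(1-rho)/3.

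**Step 3: results at 28 per arm**, with SE = 8 x sqrt(2 x factor/28) and power = Phi(6/SE - 1.96). Paired entries are planned / adjusted.

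| rho | Factor | Loss, variance scale | Loss, SE scale | SE (points) | Power | n per arm for 80% power |
|---|---|---|---|---|---|---|
| 0.3 | 1.05 / 0.56 | 47% | 27% | 2.19 / 1.60 | 0.78 / 0.96 | 30 / 16 |
| 0.5 | 0.75 / 0.50 | 33% | 18% | 1.85 / 1.51 | 0.90 / 0.98 | 21 / 14 |
| 0.7 | 0.45 / 0.36 | 20% | 11% | 1.43 / 1.28 | 0.987 / 0.997 | 13 / 11 |

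A simulation of 20,000 trials with 28 per arm gave variance losses of 45%, 32% and 18%. Both estimators centred on the true 6 points.

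**Step 4: thresholds, equal SDs.**
- The planned contrast matches the factor of 1 behind the 28 per arm when 1.5(1-rho) = 1, that is rho = 1/3 (power 0.801). Below that it falls short: 0.78 at rho 0.3 and 0.73 at rho 0.2.
- It is less precise than the mean of the two follow-ups with baseline ignored when 1.5(1-rho) > (1+rho)/2, that is rho below 1/2.

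**Step 5: sensitivity.**
- Higher correlation: the loss is 13% at rho 0.8 and 7% at rho 0.9.
- Follow-ups modelled one at a time: the loss is (1-rho)/2, or 35%, 25% and 15%.
- Narrowed baseline: patients enter only with 6 or more on the 3-item form (Participant eligibility), which may shrink the baseline SD. If it is k times the follow-up SD, the loss is (k-rho)^2 / [(1+rho)/2 + k^2 - 2k x rho]. At an assumed k = 0.8 this is 0.25/0.81 = 31%, 0.09/0.59 = 15% and 0.01/0.37 = 3%.

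**The case against.** The planned analysis is valid. It is unbiased under randomisation, and the article's statement about bias is true. Under equal SDs it keeps at least 80% power at 28 per arm once rho reaches about 1/3, and at rho 0.5 it has 90%. All of that stands, and it makes this a point about efficiency only.

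Three stronger readings are tempting, and the article does not support them.

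- A reader might infer that the model wastes a fixed 20% to 47% of the precision. That range needs rho between 0.3 and 0.7, equal SDs and pooled follow-ups, and the article states neither the correlation nor visit-specific SDs.
- A reader might infer that the trial misses its stated power, on the ground that selecting lonely patients makes a low rho likely. Such selection would lower rho by narrowing the baseline SD, which also shrinks the planned variance. With k = 0.8 and rho = 0.2 the planned factor is 0.6 + 0.64 - 0.32 = 0.92. That is below 1, so the target would still be met. A shortfall is possible but not shown.
- A reader might infer that chance baseline imbalance is ignored. It is not, because the contrast subtracts each arm's baseline mean. What it does is over-correct: given an observed baseline difference d, the estimate is shifted by (1-rho) x d in expectation. With d = 3 and rho = 0.5 that is 1.5 points, against a 6-point target.

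None of these limits reverses the direction. Apart from a trivial degree of freedom, the planned contrast is never more precise than the adjusted one. Nor can the choice be left to a separate analysis plan, since the article fixes the fixed effects and rules out covariates.

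**Conclusion.** The point holds as an avoidable loss of efficiency, not as an error of validity. The specified model makes the treatment effect a difference in differences, and the reason given for having no covariates does not bear on precision. How much is lost turns on a correlation and SD ratio that the article does not report. It could be close to half the attainable precision at low correlation with equal SDs, or a few per cent at high correlation or with a narrowed baseline. Any shortfall against 80% power is conditional in the same way. The change is worth making because it cannot materially hurt and may help a small trial appreciably, especially for outcomes with no stated power.

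**What to change.** For UCLA loneliness, COMM and every other outcome measured at baseline, do one of the following:

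- model the post-treatment scores with the participant's own baseline score of that outcome as a covariate; or
- keep all three visits in the mixed model but drop the arm main effect, so that baseline means are common across arms, and retain post and arm x post.

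The two agree only if compound symmetry holds. With a random intercept alone, the second ties the weight given to baseline to that structure, and eligibility selection makes the structure doubtful. If the second is chosen, an unstructured covariance across the three visits is preferable.

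Replace the sentence that excludes control variables with one stating the baseline adjustment and giving precision as the reason. The cost is that sentence and one degree of freedom. Table 1 already lists every effectiveness outcome as collected at baseline, so no new data or patients are needed.
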